### Sample size calculation and statistics

Sample size calculation is based on the difference in survival from our previous prophylactic haloperidol study [19]. In this study, the median survival time in the control group was 18 days. If the true hazard ratio of control patients relative to intervention patients is 0.85, taking into account an accrual time of 90 days with 28 days of follow-up, we will need to study 647 patients per intervention group and 647 control patients to be able to reject the null hypothesis that the experimental and control survival curves are equal with probability (power) 0.80. The Type I error probability associated with this null hypothesis test is 0.05. Taking into account a dropout percentage of 10%, we will include 715 patients per group (Figure 1). A fixed sequence procedure will be followed. First, the highest dosage of prophylactic haloperidol will be compared with placebo using alpha 0.05 (two-sided). Only if H_0_ is rejected, subsequently the lower dosage of prophylactic haloperidol will be compared with placebo. Cox regression analysis will be used to test differences on 28-day survival in the intervention group compared with the placebo group.

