**Methods:**

This will be a multicenter three-armed randomized, double-blind, placebo-controlled, prophylactic intervention study in critically ill patients. We will include consecutive non-neurological ICU patients, aged ≥18 years with an expected ICU length of stay >1 day. To be able to demonstrate a 15% increase in 28-day survival time with a power of 80% and alpha of 0.05 in both intervention groups, a total of 2,145 patients will be randomized; 715 in each group. The anticipated mortality rate in the placebo group is 12%. The intervention groups will receive prophylactic treatment with intravenous haloperidol 1 mg/q8h or 2 mg/q8h, and patients in the control group will receive placebo (sodium chloride 0.9%), both for a maximum period of 28-days. In patients who develop delirium, study medication will be stopped and patients will subsequently receive open label treatment with a higher (therapeutic) dose of haloperidol. We will use descriptive summary statistics as well as Cox proportional hazard regression analyses, adjusted for covariates.

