**Discussion:**

This will be the first large-scale multicenter randomized controlled prevention study with haloperidol in ICU patients with a high risk of delirium, adequately powered to demonstrate an effect on 28-day survival.

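### The 80% power for a hazard ratio of 0.85 rests on an 18-day control median that contradicts the 12% placebo mortality, and on observation beyond day 28; at 12% mortality, power is about 16% to 18%

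*Protocol article*

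**What the plan says.** Protocol article, Sample size calculation and statistics: the control-arm input comes from the group's previous prophylaxis study, "In this study, the median survival time in the control group was 18 days". The effect is worded "the true hazard ratio of control patients relative to intervention patients is 0.85", and the size follows: "taking into account an accrual time of 90 days with 28 days of follow-up, we will need to study 647 patients per intervention group", with the same number of controls, 80% power and a type I error of 0.05. A 10% dropout allowance raises this to 715 per group. Each dose is compared with placebo by Cox regression on 28-day survival, two-sided, in a fixed sequence that starts with the higher dose.

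Abstract, Methods: the same 80% power is repeated, with the target described as a 15% gain in survival time over 28 days. The next sentence but none of the calculation says: "The anticipated mortality rate in the placebo group is 12" (per cent).

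Abstract, Discussion: the trial is called "adequately powered to demonstrate an effect on 28-day survival".

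Table 1 (Definition of study objectives) limits the primary outcome to 28 days per patient.

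**The concern.** An 18-day median means that half the control patients are dead by day 18. A placebo mortality of 12% means that 88% are alive. Both cannot describe the same arm over 28 days, and the article does not reconcile them.

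There is a second, separate problem. Adding 90 days of accrual to 28 days of follow-up treats patients as observed for 28 to 118 days, depending on entry date. That suits a trial with a common closing date. Here every patient's primary outcome closes at day 28, so deaths after that day cannot count.

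The number of deaths sets the power of a Cox comparison, and both inputs inflate it. If power is far below 80%, the trial would usually miss the effect it was sized for. A neutral result could then be read as absence of benefit: the section Discussion and trial status already says that other forms of prevention need to be studied if there is no effect. The futility looks at 175, 350 and 500 patients use the same endpoint.

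**Working it through.** **Inputs.** From the sample size section: control median 18 days, hazard ratio 0.85, accrual 90 days, follow-up 28 days, two-sided alpha 0.05, power 0.80, 647 per group (715 with dropout). From the abstract: placebo mortality 12%. From Table 1: a 28-day window. Assumptions: constant hazards, uniform accrual, and the 12% read as 28-day mortality.

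**1. Deaths required.** Schoenfeld: D = 4(1.960 + 0.8416)² / (ln 0.85)² = 1,189 per pairwise comparison.

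**2. Reproducing 647.** λ = ln 2 / 18 = 0.0385 per day. With accrual A = 90 and follow-up F = 28, the probability of death is 1 − [exp(−λF) − exp(−λ(A+F))] / (λA).

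| Direction of the hazard ratio | Control | Haloperidol | n per group = D / (sum of both) |
|---|---|---|---|
| Control/haloperidol = 0.85 (literal) | 0.905 | 0.932 | 647 |
| Haloperidol/control = 0.85 (benefit) | 0.905 | 0.871 | 669 |

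The literal direction returns the article's figure. It assumes 1,189 deaths among 2 × 647 = 1,294 patients, which is 92%.

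**3. What an 18-day median implies at day 28.** 1 − 0.5^(28/18) = 66% dead, against the stated 12%.

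**4. Keep the 18-day median, stop at day 28.** Death probabilities are 0.660 (control) and 0.600 (hazard × 0.85). Deaths: 647 × 1.260 = 815, or 715 × 1.260 = 901. Power = Φ(√d/2 × 0.1625 − 1.960) = 64% or 68%.

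**5. Use 12% at day 28.** Haloperidol mortality at a hazard ratio of 0.85 is 1 − 0.88^0.85 = 10.3%.

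| Per group | Deaths | √d/2 × 0.1625 | Power | Two-proportion check |
|---|---|---|---|---|
| 647 (after 10% dropout) | 647 × 0.223 = 144 | 0.976 | 16.3% | 16.2% |
| 715 (no dropout) | 715 × 0.223 = 159 | 1.026 | 17.5% | 17.4% |

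At the final alpha of 0.049 these become 16.1% and 17.3%.

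**6. Effect detectable with 80% power at 12%.** Hazard ratio about 0.61 with 647 (12% to 7.5%), or about 0.62 with 715 (12% to 7.7%). For reference, 80% power at 0.85 would need 1,189 / 0.223, about 5,330 per group before dropout.

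**7. Other placebo mortalities (assumed values), hazard ratio 0.85.**

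| Placebo mortality at day 28 | Power, 647 | Power, 715 |
|---|---|---|
| 10% | 14% | 15% |
| 15% | 19% | 21% |
| 20% | 24% | 26% |
| 30% | 34% | 37% |

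**8. The 15% gain in survival time.** At 12% mortality, mean days alive within 28 is at least 0.88 × 28 = 24.64, even if every death fell on day 0. Then 24.64 × 1.15 = 28.3, which exceeds the window. At a constant hazard the mean is 26.3 days, and 15% more is 30.2.

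**The case against.** The best defence is that the calculation is correct for its inputs: 647 is reproduced, so there is no slip in the formula. That stands. The fault is in the inputs.

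It can also be said that the 12% carries no time point. True, but it directly follows the 28-day target. If it covered a longer period, 28-day mortality and power would be lower still. The 18 days may describe a sicker group, since the Background reports the earlier results in patients with a predicted delirium risk above 50%, whereas this trial expects a median risk of about 35%. That might explain the discrepancy, but it would also be a reason not to use 18 days as this trial's control median.

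Four stronger readings are tempting, and the documents do not support them:

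- *The 90-day accrual contradicts the 12%.* It does not; it conflicts with the 28-day outcome window.
- *The trial is sized to show harm.* Only the literal direction gives 647, but the difference from 669 is 3.4% and the Freedman formula gives 650 and 672. The direction is a minor error that leaves the conclusion unchanged.
- *The 15% gain is a separate design error.* It is unattainable if read as mean days within 28, but it is probably loose wording for the hazard ratio of 0.85.
- *A neutral result could never exclude 0.85.* With 715 per group, 12% mortality and no true effect (about 172 deaths), an observed hazard ratio between about 1.15 and 1.35 is non-significant with a 95% interval excluding 0.85. This happens about 16% of the time.

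**Conclusion.** The concern holds. The stated 80% power is not delivered for the 28-day endpoint at the article's own placebo mortality. Power for a hazard ratio of 0.85 is about 16% with 647 evaluable per group and about 18% with 715 and no dropout.

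The conflict between an 18-day median and 12% mortality needs no model if the 12% is read as 28-day. The power figures also assume proportional hazards. The conclusion is not sensitive to the exact mortality: across assumed values of 10% to 30%, power stays between 14% and 37%. Nor does it depend on rejecting the 18-day median, because the 28-day window alone brings power to 64% to 68%.

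This must be corrected, because it concerns the headline power claim for the primary endpoint.

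**What to change.** 1. Reconcile the 18-day median with the 12%: say what each describes, give the 12% a time point, and use one control-arm assumption throughout.
2. Redo the calculation on deaths within 28 days, without accrual time, with the hazard ratio defined as haloperidol relative to placebo.
3. If the size stays as it is, restate what it delivers at 12%: with 647 evaluable per group, about 16% power at 0.85 and 80% power at about 0.61 (12% to 7.5%); with 715 and no dropout, about 18% and about 0.62 (12% to 7.7%). Label which dropout assumption applies. Whether to change the target effect, the size or the endpoint instead is the sponsor's decision.
4. Remove the claim "adequately powered to demonstrate an effect on 28-day survival" from the abstract, and replace the 15% gain in survival time with the hazard ratio.
5. State that a neutral result will be interpreted through its confidence interval and not as evidence of no effect, without predicting what that interval will contain.

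Cost: rewording of the sample size section and abstract, with less favourable figures. Restating needs no extra patients; a larger trial or a new endpoint would be a design change with its own cost.

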## Discussion and trial status

This is the first large-scale multicenter randomized-controlled prevention study with haloperidol in ICU patients with an increased risk to develop delirium. The study design and protocol was finalized in 2012 and the protocol passed the medical ethical committee on February 2013. Prior to the start of the study, all centers will be visited to inform all involved researchers and a second meeting will take place as an initiation visit. Furthermore, a meeting with the DSMB and the monitor will be scheduled prior to the conduction of the study.

Results of our study will be of importance for critically ill patients and permits us to draw conclusions on the effectiveness of haloperidol prophylaxis in reducing 28-day mortality, preventing delirium, and improving delirium-related outcome. Furthermore, it will provide information regarding the delirium-risk category in which the PRE-DELIRIC model prophylaxis is most effective. Positive effects of haloperidol prophylaxis on delirium outcome will result in the alteration of daily practice for critically ill patients and would therefore have major implications. However, if there is no effect of haloperidol prophylaxis, other possibilities of delirium prevention, such as nursing interventions, need to be studied. In addition, the effectiveness of nursing interventions focusing on delirium prevention can be studied in conjunction with haloperidol prophylaxis.

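### The sample size rests on an 18-day control median survival, but the protocol expects 12% placebo mortality; at 12% by day 28 the power for HR 0.85 is about 16–18%, not 80%

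*Protocol article*

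**What the plan says.** The section Sample size calculation and statistics takes its control survival from the group's previous haloperidol study: "In this study, the median survival time in the control group was 18 days". The effect to be detected is introduced with the words "If the true hazard ratio of control patients relative to intervention patients is 0.85". The calculation then allows for 90 days of accrual plus 28 days of follow-up, and its result is that "we will need to study 647 patients per intervention group and 647 control patients" for 80% power against the hypothesis of equal survival. Alpha is 0.05 two-sided, and a 10% dropout allowance brings the figure to 715 per group. The high dose is tested against placebo first; the low dose is tested only if that test is significant.

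The abstract (Methods) repeats the 80% power and 715 per group, and then says "The anticipated mortality rate in the placebo group is 12" per cent. The abstract (Discussion) calls the trial "adequately powered to demonstrate an effect on 28-day survival". The primary endpoint is 28-day survival (Tables 1 and 2). Discussion and trial status looks ahead to a negative result: "if there is no effect of haloperidol prophylaxis, other possibilities of delirium prevention, such as nursing interventions, need to be studied".

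**The concern.** The 18-day median is used as the control survival of this trial, and the 12% is the mortality expected in this trial's placebo group. A trial in which half the controls die by day 18 is not a trial in which 12% of them die. No part of the article reconciles the two or states how many deaths are needed.

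This matters because the power of a log-rank or Cox comparison is set by the number of deaths, not the number of patients. If the 12% is closer to the truth, the trial has a small fraction of the information that the 80% claim requires. A real effect of the planned size would usually be missed. The fixed sequence would then usually stop at the high dose, leaving the low dose without a confirmatory test. A non-significant result would also say little about whether haloperidol works.

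**Working it through.** **Inputs.** From Sample size calculation and statistics: control median 18 days, HR 0.85, accrual A = 90 days, follow-up F = 28 days, power 0.80, two-sided alpha 0.05, 647 per group (715 with dropout). From the abstract: placebo mortality 12%. Its horizon is not stated; day 28 is assumed here and varied in step 5.

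**1. Deaths needed (Schoenfeld, 1:1).** 4 × (1.960 + 0.842)² / (ln 0.85)² = about 1,189 per pairwise comparison.

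**2. Reproducing 647.** Assume exponential survival with λ = ln 2 / 18 and uniform accrual. The probability of death is p = 1 − exp(−λF) × (1 − exp(−λA)) / (λA).
- Control: p = 0.905.
- Intervention, with the HR as worded (control relative to intervention, so hazard λ/0.85): p = 0.932.
- Patients per group: 1,189 / (0.905 + 0.932) = 647, an exact match.
- With the HR in the favourable direction (0.85λ): p = 0.871 and 669 per group.

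So 647 assumes that about 92% of patients die, and it counts deaths up to 118 days after entry.

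**3. What each input implies at day 28.**
- Median 18 days: 1 − 2^(−28/18) = 66.0% dead. Without the exponential assumption, at least 50%.
- 12% dead at day 28: exponential median = 28 × ln 2 / (−ln 0.88) = about 152 days.

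**4. Power at 12% day-28 mortality.** With HR 0.85 favouring haloperidol, intervention mortality is 1 − 0.88^0.85 = 10.3%. Power = Φ(0.1625 × √deaths / 2 − 1.96).

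| Per group | Deaths in two arms | Power |
|---|---|---|
| 647 | 647 × 0.2230 = 144.3 | 16.3% |
| 715 | 715 × 0.2230 = 159.4 | 17.5% |

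A two-proportion calculation gives 16.2% and 17.4%. At the final alpha of 0.049, the log-rank figures are 16.0% and 17.3%.

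**5. Sensitivity (647 to 715 per group).**
- Placebo mortality at day 28 of 10%: 14–15%. Of 15%: 19–21%. Of 20%: 24–26%. Of 30%: 34–37%.
- HR in the direction worded (intervention mortality 14.0%): 18–20%.
- Effect read as a 15% relative reduction in mortality (12% to 10.2%): 17.6–19.0%.

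**6. What the trial can detect at 12%.** For 80% power the hazard ratio must be about 0.61 (647 per group) or 0.62 (715 per group), that is 12% against about 7.5–7.7%.

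**7. Precision if there is no effect.** With 647 per group and 12% in both arms there are 647 × 0.24 = 155 deaths. The 95% interval around HR 1.0 is exp(±1.96 × 2/√155), about 0.73 to 1.37.

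**8. Accepting the 18-day median but counting deaths only to day 28.** In the favourable direction 647 × (0.660 + 0.600) = 815 deaths, power 64%. In the direction worded 647 × (0.660 + 0.719) = 892 deaths, power 68%. The section's own method would need 862–943 per group.

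**The case against.** The strongest defence is that the two figures describe different populations. The 18 days comes from an earlier cohort that the Background describes as having a predicted delirium risk above 50%, whereas this trial expects a median risk of about 35%. Both figures could be true of their own patients, and what the 18 days measured in the source cannot be checked here. That explains the mismatch but does not repair the power: the section uses the historical figure as the control survival of this trial, whose own expected mortality is 12%.

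Second, the 12% carries no time horizon, so 16–18% is conditional on day 28. This is fair and should be stated. The 12% does follow directly on the 28-day power statement, and the primary endpoint is 28-day mortality. Step 5 shows that no plausible shift brings power near 80%. Even 50% mortality at day 28 would give only 52–56%.

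Third, the 66% depends on exponential survival. True, but the contradiction does not: a median of 18 days means half are dead by then under any model.

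Fourth, the remark in Discussion and trial status concerns next research steps if there is no effect; it does not say that a non-significant P value will be read that way. That stands. A rule for reading a non-significant result is therefore good practice rather than the correction of an error.

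Fifth, replacing the median alone would not be enough. With the 90-day accrual term left in, the same method at 12% would show about 32% (647) or 35% (715), because it counts deaths after day 28. This is a second fault in the paragraph and belongs in the fix.

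**Conclusion.** The concern holds. The arithmetic that leads to 647 can be reproduced, but its control-survival input conflicts with the mortality the protocol itself expects. If placebo mortality is 12% at day 28 and the hazards are proportional with HR 0.85 in favour of haloperidol, the power per comparison is 16.3% (647 per group) to 17.5% (715 per group). That comes from 144 to 159 deaths where about 1,189 are needed, so the planned effect would be missed about five times in six. Over the other readings of the 12% scenario the range is 16–20%, and with 15–20% mortality it is 19–26%. The 80% is not reached under the 18-day median either once deaths are counted only to day 28, where 647 per group gives 64–68%.

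The claim of adequate power in the abstract is therefore wrong as written. If haloperidol truly had no effect, the expected interval of about 0.73 to 1.37 would exclude neither the planned 0.85 nor the 0.8 that the Background reports from the earlier study.

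**What to change.** - In Sample size calculation and statistics, replace the 18-day median with the expected placebo mortality at day 28, and state the horizon of the 12% there and in the abstract.
- Remove the 90-day accrual term, since each patient contributes to the primary endpoint only to day 28.
- State the direction of the hazard ratio. As worded, 0.85 puts the higher hazard in the intervention arm.
- Give the expected number of deaths per comparison and the resulting power: at 12%, about 16–18% for HR 0.85. Alternatively, state the detectable effect: HR about 0.62 with 715 per group.
- Delete the claim of adequate power from the abstract, and correct the 80% wherever it appears.
- Advisable, though less essential: say that a non-significant primary result is inconclusive unless the confidence interval excludes HR 0.85.

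The cost is a rewritten paragraph, a corrected abstract and a much less favourable power figure. For scale, 80% power at 12% mortality would take about 1,189 / 0.2230 = 5,330 evaluable patients per group. That enlargement is not being requested.

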### Objectives

Definitions of variables in objectives are reported in Table 1.

**Table 1 T1:** Definition of study objectives

**Objective**	**Definition**
*Survival days in 28 days*	Number of days that patients survive in 28 days. All patients will be classified as either ‘alive at study day 28’ or, if dead, ‘dead at study day 28’ on an intention-to-treat basis.
*Delirium diagnosis*	Patients are diagnosed as delirious when they have at least one positive CAM-ICU screening during their complete ICU stay. Patients who were not delirious during their ICU-stay are considered as non-delirious patients.
*Delirium-and-coma-free days in 28 days*	Number of days that the patient is alive and not delirious and not in coma over 28 days starting from the day of inclusion. A delirium-and-coma-free day is defined as a negative CAM-ICU screening with a Richmond Agitation Sedation Score (RASS) greater than (more alert than) -3/-4/-5 during a day. In case a delirious patient is discharged to the ward, a delirium-free day is defined as a delirium observation scale score [30] of less than 3 during a complete day.
*Duration of mechanical ventilation*	Time in days that the patient is on the mechanical ventilator. If the patient is ventilated mechanically several times during one ICU admission, then the ventilator times are added. Both invasive and non-invasive ventilation will be registered. Ventilator-free days (in 28 days) will be calculated.
*Incidence of re-intubation*	Patients who need to be intubated within 28 days from randomization, following a previous extubation, irrespective of the reason for re-intubation, are counted as incident case for re-intubation.
*Incidence of ICU readmission*	Patients who need to be readmitted to the ICU during within 28 days from randomization, irrespective of the reason for readmission, are counted as incident cases for ICU readmission.
*Side effects*	Drowsiness, agitation, QTc-time prolongation (using 12-leads ECG or monitor strip with Bazett’s formula) and development of extra pyramidal symptoms such as tandem gait, dystonia, tremor, myoclonus, tics, rigidity, akathisia [31], determined daily by physical examination by the intensivist.
*Serious adverse event*	Any untoward medical occurrence or effect at any dose that results in one of the following outcomes and is not classified as a clinical outcome of delirium or the underlying disease using the description above:

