	- death that is not related to the underlying disease or sequel of the underlying disease, or death that is considered by the investigator to be related to study drug
	- prolonged inpatient hospitalization or re-hospitalization
	- a life-threatening experience (that is, immediate risk of dying)
	- persistent or significant disability/incapacity
	- congenital anomaly/birth defect
	- considered significant by the investigator for any other reason
*Sudden unexpected serious adverse reactions*	Unexpected adverse reactions are adverse reactions, of which the nature, or severity, is not consistent with the applicable product information. Adverse reactions are all untoward and unintended responses to an investigational product related to any dose administered.

#### **
*Primary objective*
**

To determine the effect of prophylactic haloperidol use on 28-days survival.

#### **
*Secondary objectives*
**

There are seven secondary objectives:

1. To determine the effect of prophylactic haloperidol use on 90-day survival; survival analysis stratifying for delirium incidence will be performed.

2. To determine the effect of prophylactic haloperidol use on the incidence of delirium.

3. To determine the effect of prophylactic haloperidol use on the number of delirium- and coma-free days in a period of 28 days.

4. To determine the effect of prophylactic haloperidol use on delirium related outcomes: time to successful extubation, incidence of re-intubation, incidence of ICU readmission, and incidence of unplanned removal of tubes and catheters.

5. To evaluate the incidence and severity of side effects of haloperidol prophylaxis.

6. To determine the effect of preventive haloperidol use on quality of life 1 and 6 months following ICU admission compared with a baseline measurement at ICU admission using the Short Form-12 (SF-12) questionnaire.

7. *A priori* defined post-hoc analyses:

a. To determine the preventive effectiveness of haloperidol in different patient groups based on the *a priori* risk to develop delirium: patients with a predicted risk up to 50%, 50–70%, 70–90%, above 90% will be evaluated.

a. To determine the preventive effectiveness of haloperidol in different patient groups: medical/surgical/trauma patients, per acute physiology and chronic health evaluation-II (APACHE-II) score (<20, 20–25, >25)

a. Effectiveness of prophylaxis when delirium is diagnosed based on 1, 2, or more days with positive CAM-ICU scoring.

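### The 647 per group counts deaths over 28 to 118 days of follow-up, but the primary endpoint ends at day 28; on the plan's own inputs power is 64–68%, not 80%

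*Protocol article*

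**What the plan says.** The section Sample size calculation and statistics gives these inputs:

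- Control survival: "the median survival time in the control group was 18 days".
- Effect: "If the true hazard ratio of control patients relative to intervention patients is 0.85".
- Time frame: "taking into account an accrual time of 90 days with 28 days of follow-up".
- Result: "we will need to study 647 patients per intervention group and 647 control patients", at power 0.80 and type I error 0.05. The first comparison is stated to be two-sided.
- A 10% dropout allowance takes the number to 715 per group.

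The primary endpoint has a fixed horizon. Under Objectives, Table 1 defines survival days as "Number of days that patients survive in 28 days" and classifies each patient as alive or dead at study day 28. The primary objective reads "To determine the effect of prophylactic haloperidol use on 28-days survival". Table 2 (Data collection) lists 28-day mortality as the primary endpoint. The sample size section plans Cox regression on 28-day survival, and the interim futility and superiority looks use the same endpoint. Survival to 90 days is secondary only.

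**The concern.** Accrual time enters a survival sample size when patients are followed until a common calendar date, because those enrolled early then contribute longer follow-up and more deaths. With a horizon fixed at 28 days from randomisation it has no role: each patient contributes the same 28 days whether recruitment takes three months or three years. Including a 90-day accrual period therefore suggests that 647 was calculated for a different trial, with deaths counted that the primary analysis will never see. If so, the stated power is overstated even when every other input is accepted. The abstract's description of the trial as adequately powered for 28-day survival would then fail on the plan's own assumptions, and any later recalculation that reused the setting would carry the same inflation.

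**Working it through.** **Inputs** (all from Sample size calculation and statistics): control median 18 days, hazard ratio 0.85 worded as control relative to intervention, accrual A = 90 days, further follow-up F = 28 days, power 0.80, two-sided alpha 0.05. Exponential survival and uniform accrual are assumed.

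**Step 1. Deaths required (Schoenfeld, 1:1).**
4 × (1.960 + 0.842)² / (ln 0.85)² = 1,188.7, so 1,189 deaths over two groups.

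**Step 2. Reproduce 647.** The probability of an observed death is p = 1 − [exp(−hF) − exp(−h(A+F))] / (hA).

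- Control: h = ln 2 / 18 = 0.0385 per day, p = 0.905.
- Intervention, hazard ratio as printed: h / 0.85 = 0.0453 (median 15.3 days), p = 0.932.
- Mean p = 0.9185; 1,188.7 / (2 × 0.9185) = 647.0 per group.

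This matches the printed figure. Alternatives do not:

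| Setting | Per group, direction as printed | Per group, benefit direction |
|---|---|---|
| 90 days accrual + 28 days | **647** | 669 |
| 62 days accrual + 28 days (90 in total) | 669 | 699 |
| Fixed 90 days for everyone | 609 | 620 |
| Fixed 28 days for everyone | 862 | 944 |

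In the setting that fits, follow-up runs from 28 days (last patient enrolled) to 118 days (first), with mean (28 + 118)/2 = 73 days, and about 92% of patients are expected to die under observation.

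**Step 3. Censor every patient at day 28.** Now p = 1 − exp(−28h). Power is Φ(√deaths × |ln 0.85| / 2 − 1.960).

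| Direction of 0.85 | p control / intervention | Deaths at 647 per group | Power under 90 + 28 | Power to day 28 |
|---|---|---|---|---|
| As printed | 0.660 / 0.719 | 892 | 80.0% | 68.0% |
| Benefit of haloperidol | 0.660 / 0.600 | 815 | 78.7% | 64.1% |

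Log-rank simulation with 3,000 runs gave 67.6% and 64.3% for the last column.

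Deaths counted by the formula but lying outside the endpoint:

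- Printed direction: 1,189 − 892 = 297 (25%).
- Benefit direction: 1,149 − 815 = 334 (29%).

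If all 715 per group were evaluable, power to day 28 would be 72.3% (printed) or 68.4% (benefit).

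**Step 4. Is this separate from the 18-day median?** The abstract anticipates 12% placebo mortality, which corresponds to h = −ln(0.88)/28 = 0.00457 per day. For a benefit of 0.85 with 647 per group:

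- Keeping 90 + 28 days: 337 deaths, apparent power 32%.
- Censoring at day 28: 144 deaths, power 16% (18% with the direction as printed).

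Correcting only the mortality input would still leave the apparent power at about twice the true value.

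**The case against.** The arithmetic is not in dispute. The strongest objection is one of proportion. The 18-day median implies that 66% of controls die by day 28, against 12% in the abstract, so 64–68% power describes no plausible version of this trial. The mortality input does more damage, and one recalculation could settle both. That is fair as to ranking. It also means that the fix must not end with 64–68% printed as the new power. It does not remove the point, because censoring at day 28 is needed whichever mortality figure is used.

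Three narrower points stand as qualifications:

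- In the benefit direction the 90 + 28 setting already gives 78.7%, so the like-for-like loss is from 78.7% to 64.1%. The remaining 1.3 points below 80% come from the direction of the hazard ratio.
- Follow-up of 118 days is the maximum, not typical; the mean is 73.
- The comparison of 32% with 16% is illustrative. No document proposes that calculation, and it assumes that the hazard stays constant to day 118.

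It can also be said that 28 days of follow-up, read alone, agrees with the endpoint, so the mismatch is inferred. The inference is strong: the accrual period is stated as an input, the standard formula returns 647.0, and a fixed 28-day horizon does not come near it. Nor is this something left to a fuller document, since the article prints the assumption and the result.

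**Conclusion.** The concern holds. The 647 per group and the 80% power belong to a design with follow-up to the end of accrual plus 28 days. The planned primary analysis stops at day 28. On the plan's own median and hazard ratio, 647 evaluable per group gives 68% power in the direction printed and 64% for a benefit of haloperidol; 715 per group without any loss gives 72% or 68%. Reaching 80% on those inputs would need about 862 or 944 per group. These figures rest on exponential survival and uniform accrual, the assumptions under which the plan's figure is reproduced. They keep the 18-day median only to isolate this error; at 12% mortality the power to day 28 is 16–18%.

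**What to change.** In Sample size calculation and statistics, delete the 90-day accrual term and state that every patient is censored at day 28 from randomisation. Recalculate on that basis and report the power that 647 evaluable (715 randomised) per group provides, giving the direction of the hazard ratio explicitly. Reconcile the 18-day median with the 12% mortality in the abstract in the same step, so that the restated power is not again tied to an input that the article contradicts. Bring the power statements in the abstract into line.

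The cost is protocol wording and one calculation, and the stated power will be less favourable. No increase in sample size is requested.
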